## 1 Study Protocol

---

| Title                          | Cognitive behavioural therapy for the treatment of late life depression – a multicentre, randomized, observer-blinded, controlled trial (CBTlate)                                                                                                                                                                                                                                                                                                                                                                                                                                                      |
| Trial Design                   | Randomized, multi-center, single blind (observer-blinded), active-controlled, parallel group trial (therapeutic confirmatory) in 248 patients with late-life depression of both genders.                                                                                                                                                                                                                                                                                                                                                                                                               |
| Condition                      | Late life depression (age $\geq$ 60 years)                                                                                                                                                                                                                                                                                                                                                                                                                                                                                                                                                             |
| Objective                      | To test the hypothesis that a 15-session individually-delivered cognitive behavioural therapy (CBT) specific for late life depression (LLD) is of superior efficacy in reducing symptoms of depression in comparison with a supportive unspecific intervention (SUI) of the same quantity in patients with LLD                                                                                                                                                                                                                                                                                         |
| Time plan                      | First patient first visit (FPFV): Q2/2018
Recruitment period: Q2/2018 – Q2/2020
Last patient last visit (LPLV): Q2/2020
Trial report: Q1/2021                                                                                                                                                                                                                                                                                                                                                                                                                                                 |
| Trial sites                    | Number of trial sites: up to 7
Number of countries: 1 (Germany)                                                                                                                                                                                                                                                                                                                                                                                                                                                                                                                                     |
| Trial population               | To be assessed for eligibility: n = 300
To be allocated to trial: n = 248
To be analysed: n = 248 ITT, n =198 PP                                                                                                                                                                                                                                                                                                                                                                                                                                                                                 |
| Treatment(s) / Intervention(s) | 
Experimental intervention: A manual-based, individual,15-session, twice weekly, outpatient CBT specifically designed for patients with late life depression.
 
Control intervention: A manual-based 15-session, twice weekly, outpatient standard treatment containing supportive and educational elements (supportive unspecific intervention, SUI).
 
Duration of intervention per patient: 8 weeks.
 
Follow-up per patient: 6 months after randomization.
                                                                                        |
| Inclusion criteria             | Participating patients have to fulfil the following inclusion criteria: 
 
• out-patient status
 
• male/female of age <math>\geq</math> 60 years
 
• depressive episode (moderate to severe according to ICD-10)
 
• GDS > 10, QIDS-C > 10
 
• MMST > 25 points
 
• no or stable (<math>\geq</math> 6 weeks) antidepressive pharmacological treatment at baseline
 
• no or stable antidepressive pharmacological treatment during 8-week intervention
 
• sufficient German language skills
 
 |

**Exclusion criteria**

Any of the following will exclude a patient from the trial:

- Bipolar depression
- Schizophrenia
- Other psychotic disorder
- Substance abuse or dependency
- Dementia
- Acute suicidality
- Anxiety disorder as stand-alone diagnosis (e.g. generalized anxiety disorder, panic disorder, social phobia)
- Obsessive-compulsive disorder (OCD) as stand-alone diagnosis
- Participation in any other clinical trial parallel to this trial
- Additional psychological/psychotherapeutic treatment throughout the treatment period
- Regular use with scheduled dosing of Benzodiazepines (not PRN)
- Severe medical condition, which clearly impacts on depression or on the ability to participate in the trial
- Brain disease with severe functional impairment that impacts the ability to participate in the trial (e.g. aphasia, Parkinson's disease)

**Outcome(s)**

The primary efficacy endpoint is the change in Geriatric Depression Scale (GDS) from baseline (T0) to end-of-treatment (T2).

Key secondary endpoint(s) is the change in Geriatric Depression Scale (GDS) from baseline to end of follow-up (T3) as well as changes from baseline to end-of-treatment (T2) and to end of follow-up (T3; 6 months after randomization) in:

- Quick Inventory of Depressive Symptomatology (QIDS-C)
- Geriatric Anxiety Inventory (GAI)
- Patient-Reported Outcome in Major Depressive Disorder (PRO-MDD)
- WHO Quality of Life (WHOQOL-OLD, WHOQOL-BREF)
- Health Status (SF 36)
- Insomnia Severity Index (ISI)
- Epworth Sleepiness Scale (ESS)
- REM Sleep Behavior Disorder Screening Questionnaire (RBDSQ)
- Consortium to Establish a Registry for Alzheimer's Disease neuropsychological battery (CERADplus)
- Subtest of the Neuropsychological Assessment Battery (NAB)

The influence of traumatic experiences, and personality traits on the change in GDS will be assessed at baseline by:

- Childhood Trauma Questionnaire (CTQ-SF)
- Big Five Inventory-10 (BFI-10)

The longitudinal evaluation of depressive symptoms will be conducted by the Longitudinal Interval Follow-up Evaluation (LIFE) at follow-up (T3).

Assessment of safety:

- AE and SAE recordings
- assessment of suicidality

**Schedule**

Screening and baseline visit (T0): week 1 (visit 1)

Treatment period: 8 weeks (15 sessions)

First Outcome assessment (T1): week 5 (visit 9, after 7 therapy sessions)

Second Outcome assessment (T2): week 10 (visit 18, after completion of 15 therapy sessions)

Follow-up period: 6 months (after randomization)

Final examination: 6 months after randomization (visit 19)

|                             |                                                                                                                                                                                                                                                                                                                                                                                                                                                                                                                                                                                                                                                                                                                                                                                                                                                                                                                                                                                                                                                                                                                                                                                                                                                                                                                                                                                                                                                                                                                                                                                                                                                                                                                                                                                                                                                                                                                                    |
|-----------------------------|------------------------------------------------------------------------------------------------------------------------------------------------------------------------------------------------------------------------------------------------------------------------------------------------------------------------------------------------------------------------------------------------------------------------------------------------------------------------------------------------------------------------------------------------------------------------------------------------------------------------------------------------------------------------------------------------------------------------------------------------------------------------------------------------------------------------------------------------------------------------------------------------------------------------------------------------------------------------------------------------------------------------------------------------------------------------------------------------------------------------------------------------------------------------------------------------------------------------------------------------------------------------------------------------------------------------------------------------------------------------------------------------------------------------------------------------------------------------------------------------------------------------------------------------------------------------------------------------------------------------------------------------------------------------------------------------------------------------------------------------------------------------------------------------------------------------------------------------------------------------------------------------------------------------------------|
| Course of the trial  | Flowchart in section 12.1.                                                                                                                                                                                                                                                                                                                                                                                                                                                                                                                                                                                                                                                                                                                                                                                                                                                                                                                                                                                                                                                                                                                                                                                                                                                                                                                                                                                                                                                                                                                                                                                                                                                                                                                                                                                                                                                                                                         |

| Statistical Analysis | 
Sample size: 300 (to be screened)
 
Trial population:
Full-analysis-set population (FAS, Intention-to-treat population): 248
 
Per-protocol-set population (PPS):
198
(defined as a subset of the FAS population patients without major protocol violations.)
 
Efficacy / test accuracy: The evaluation is based on change on the GDS with a range of 0-30 points.
 
Description of the primary efficacy analysis and population: The primary (full) analysis set (FAS) is derived from the intention-to-treat principle (all subjects randomized with a valid baseline assessment and at least one valid follow-up outcome assessment). The change in GDS from baseline to end-of-treatment is evaluated by means of a mixed model for repeated measures (MMRM) with fixed effects group, time, group*time, therapist and baseline value; corresponding treatment contrasts are based on marginal means. To assess the impact of up to 20% attrition multiple imputation approaches are taken, accounting for proxy measures and assuming specific missingness-not-at-random patterns. The details are documented in a statistical analysis plan. Analysis of subjects essentially observed and treated per protocol (PP) is supportive. Subgroup analysis is done i.a. by gender and disease severity (moderate, severe).
 
Safety: Adverse events are listed and summarized by group and category, seriousness, severity, relatedness, respectively.
 
Secondary endpoints: Quantitative outcomes are summarized by mean, standard deviation and percentiles (i.e. 0, 25, 50, 75, 100), qualitative outcomes by count (percentage). Differences between treatment groups and changes over time are essentially evaluated along the same line as for the primary outcome measure, i.e. using mixed modeling (or GEEs).
 |

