### 1.10.2.3 Inclusion criteria

Participating subjects have to fulfil the following criteria:

| Inclusion Criteria                                                             |
|---------------------------------------------------------------------------------------|
| • out-patient status                                                                  |
| • male/female, age $\geq 60$ years                                                    |
| • depressive episode (moderate to severe according to ICD-10)                         |
| • Geriatric Depression Scale (GDS) $> 10$                                             |
| • Quick Inventory of Depressive Symptomatology (QIDS-C $> 10$ )                       |
| • MMST $> 25$ points                                                                  |
| • no or stable ( $\geq 6$ weeks) antidepressive pharmacological treatment at baseline |
| • no or stable antidepressive pharmacological treatment during 8-week intervention    |
| • sufficient German language skills                                                   |
| • written informed consent signed                                                     |

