##### 1.10.4.3 Premature termination of the trial

The trial will be stopped for the individual study participant, if the individual:

- Withdraws the informed consent.
- Develops a medical condition, which prevents participation in the trial.
- Experiences worsening of depression, which requires inpatient treatment or change of antidepressive medication.
- Develops acute suicidality.

The trial may be prematurely terminated by the respective competent local EC or the Lead Principal Investigator, if:

- The perception of the benefit/risk ratio becomes unfavourable for the continuation of the trial.
- The risk-benefit balance for the trial subject changes markedly.
- It is no longer ethical to continue treatment.
- It is no longer practicable to complete the trial.

However, our trial and study protocol are not to be expected to harm any subject but to improve outcomes. We do not expect that the trial has to be stopped in advance.

A decision to cease the trial is binding on all Investigators. Clinical Trials Centre Cologne, as well as the principal Investigators in each centre, must be informed immediately on the discontinuation of the trial. If the trial is prematurely terminated or suspended for any reason, the Investigator should promptly inform the subjects, should assure appropriate follow-up for the subjects, and inform the institution where the trial was being performed.

Participating centres, which fail to include the estimated number of subjects or to guarantee treatment in accordance to study protocol, will be closed.

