| a)                                                      | Concomitant medication | Recording of any concomitant medication after signature of informed consent at baseline.                                                                                                                                                                                                                                                                                                                                                                                                                                                                                                                         |
| b)                                                      | SAEs, AEs              | Recording of any spontaneously reported or observed SAEs and AEs after signature of informed consent until end of trial.                                                                                                                                                                                                                                                                                                                                                                                                                                                                                         |
| Voluntary procedures (after separate consent is given): |                        |                                                                                                                                                                                                                                                                                                                                                                                                                                                                                                                                                                                                                  |

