#### 1.11.3.2 Enrollment and enrollment visit

The screening/enrollment visit includes the information of subjects and informed consent, the assessment of demographic data, concomitant medication and diseases. Furthermore, following measurements will be obtained in order to assess the inclusion and exclusion criteria:

- Structured clinical interview (M.I.N.I. for DSM-5, Mini International Neuropsychiatric Interview German Version 7.0.2)
- Geriatric Depression Scale (GDS)
- Quick Inventory of Depressive Symptomatology Clinician-Rated Version (QIDS-C)
- Mini-Mental-Status-Test (MMST)

Subjects who are eligible to participate in the study will undergo an assessment of the medical history, psychiatric and psychotherapeutic history, history of cognition (subjective cognitive decline) and the following procedures at baseline (T0):

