### 2.6.3 Primary analysis

The primary objective of this study is to test the hypothesis that a 15-session individually delivered cognitive behavioural therapy (CBT) specific for late life depression (LLD) is of superior efficacy in reducing symptoms of depression in comparison with a supportive unspecific intervention (SUI) of the same quantity in subjects with LLD.

The primary outcome measure „change in GDS from baseline to end-of-treatment (week 10)“ is evaluated by a mixed model for repeated measures (MMRM) with fixed effects baseline, therapist, group, time and the interaction group\*time (ARH1-structured covariance matrix over time) with corresponding marginal means and contrast tests. Data from low recruiting therapists (i.e. < 4 subjects) are pooled by study centre. (In a supplementary analysis all therapists are pooled by centre.) The potential clustering of observations of participants by therapist or centre will be investigated by multilevel modelling. Since mixed models can be expected to yield valid results only in case of missingness-at-random, multiple imputation approaches are taken to assess the robustness of the results. Specifically, missing values due to death, illness or chance are separately imputed assuming mixtures of missingness-not-at-random patterns. Imputation data sets are post-processed by multiplication with factors and addition of offsets (tipping point analysis). Proxy measures are taken into account to ameliorate the effects of attrition.

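### Baseline QIDS-C and antidepressant use are available before randomisation but are not in the primary model; adding them is a cheap change that may give a small gain in precision

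*Combined protocol and SAP*

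**What the plan says.** The synopsis, protocol 1.14.3 (Primary Endpoint) and SAP 2.6.3 describe one primary model. The synopsis specifies it "with fixed effects group, time, group*time, therapist and baseline value". The SAP gives it "with fixed effects baseline, therapist, group, time and the interaction" of group and time. Therapist is a fixed effect, with therapists who have fewer than four subjects pooled by centre. Apart from baseline GDS, no patient characteristic enters, and no reason is given for stopping there.

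Two further baseline variables are on file before allocation:

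- **QIDS-C.** The screening instruments in protocol 1.11.3.2 include the "Quick Inventory of Depressive Symptomatology Clinician-Rated Version (QIDS-C"), and protocol 1.10.2.3 requires a score above 10 for entry. Every eligible patient therefore has a value.
- **Antidepressant use.** Protocol 1.10.2.3 requires no or stable "antidepressive pharmacological treatment at baseline". The notes to Table 2 (protocol 1.11.2) provide for "Recording of any concomitant medication after signature of informed consent at baseline".

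Randomisation follows the baseline assessment (protocol 1.11.3) and is stratified by centre only (protocol 1.14.2, SAP 2.1.5). The sample size section (protocol 1.14.1) itself expects adjustment for baseline to raise power, but puts no figure on it.

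**The concern.** A prespecified covariate that is measured before allocation and predicts the outcome removes variance from the residual. It does so without threatening the validity of the treatment contrast. QIDS-C is a clinician's rating of the same illness that the GDS measures by self-report, so its measurement error is at least partly separate. Antidepressant use divides the sample into two groups that may have different outlooks. If either variable predicts week-10 GDS after baseline GDS is accounted for, the present model leaves that information unused.

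Missing data are a second, smaller consideration. The plan expects up to 20% attrition, and protocol 1.10.4.3 stops participation for a patient who "Experiences worsening of depression, which requires inpatient treatment or change of antidepressive medication". Baseline clinician-rated severity and medication status could be related to such exits. A model or imputation that conditions on them might then make missing-at-random somewhat more plausible.

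What is at stake is some precision in the primary estimate, and a choice that counts as prespecified only if it is made before unblinding.

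**Working it through.** **Inputs from the plan (protocol 1.14.1, SAP 2.1.7).** Target difference 2.5 GDS points; d = 0.4; two-sided 5%; 80% power; 99 per arm evaluable; 20% attrition; 124 per arm randomised; assumed pre-post correlation 0.5.

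**Reproducing the plan's figures.**
- Implied SD: 2.5/0.4 = 6.25.
- Required n: the normal approximation gives 99 per arm and the noncentral t solution is 99.08. Noncentral t power at 99 per arm is 79.97%.
- Attrition: 99/0.8 = 123.75, rounded up to 124.
- Standard error: 6.25 × √(2/99) = 0.888.

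The stated sample size reproduces.

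**Effect of further covariates.** Let R² be the share of residual variance that the added covariates explain beyond baseline GDS. The documents give no value, so the values below are assumptions. The formulas are SE = 6.25 × √(1 − R²) × √(2/99) and equivalent n per arm = 99/(1 − R²). Power is by noncentral t at 99 per arm.

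| Assumed R² | SE (GDS points) | Power for 2.5 points | Equivalent n per arm |
|---|---|---|---|
| 0 | 0.888 | 80.0% | 99 |
| 2% | 0.879 | 80.8% | 101.0 |
| 5% | 0.866 | 81.9% | 104.2 |
| 10% | 0.843 | 83.9% | 110.0 |

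Over both arms, the last three rows are worth about 4, 10 and 22 extra evaluable patients.

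**What R² might QIDS-C supply?** Let r be its correlation with baseline GDS and s its correlation with end-of-treatment GDS. Take the plan's 0.5 for baseline GDS with later GDS, which the plan states for the interval to 6 months rather than to week 10. Then

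partial R² = (s − 0.5r)² / [(1 − r²) × 0.75].

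With assumed r and s:
- r = 0.6, s = 0.3: (0.3 − 0.3)² = 0, so 0%
- r = 0.5, s = 0.3: 0.0025/0.5625 = 0.4%
- r = 0.6, s = 0.4: 0.01/0.48 = 2.1%
- r = 0.5, s = 0.4: 0.0225/0.5625 = 4.0%
- r = 0.6, s = 0.5: 0.04/0.48 = 8.3%
- r = 0.5, s = 0.5: 0.0625/0.5625 = 11.1%

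The last two lines need baseline QIDS-C to predict later GDS as well as baseline GDS does.

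**Check on another starting SD.** The pilot's post-treatment SDs (6.42 with n = 27, 7.58 with n = 25) pool to √[(26 × 6.42² + 24 × 7.58²)/50] = 7.00. With the 0.5 correlation, the residual SD after baseline adjustment is 7.00 × √0.75 = 6.06. By the normal approximation, power at 99 per arm is then 82.7% with no further covariates and 84.5% with an added R² of 5%. The gain is again about 2 points.

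**The case against.** The strongest reply is that this is a preference and not a fault. The model already contains the baseline value of the outcome. It also contains therapist, with low recruiters pooled by centre, which largely absorbs the randomisation stratum. The three places that state the model agree, and the trial reaches its power on its own inputs. QIDS-C is cut off at entry just as the GDS is (both above 10) and overlaps with it, so it may add little. All of this stands. It limits the size of the gain but does not argue against taking it.

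Three stronger readings are tempting, and the documents do not support them.

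- **That precision is demonstrably being lost.** A reader might infer this from the table above, but every positive row rests on an assumed R², and plausible correlations give zero.
- **That the missing-at-random assumption is deficient without these covariates.** The repeated-measures model also conditions on the GDS observed at T1 (week 5). The removal rules in protocol 1.10.3 and 1.10.4.3 turn on worsening or a change of medication after entry, which is not the same variable as baseline use. Protocol 1.10.4.2 asks investigators to attempt follow-up assessments after drop-out. SAP 2.6.3 adds multiple imputation under missing-not-at-random patterns, a tipping-point analysis and proxy measures. Those are sensitivity analyses and do not change the primary model's assumption, but they limit the consequence. Nothing in the documents shows that drop-out depends on either variable.
- **That chance imbalance in antidepressant use biases the contrast.** Assume 50% use and a 2-point difference in outcome beyond baseline GDS. The SD of the imbalance at 124 per arm is √(2 × 0.25/124) = 0.0635, so a 2-SD imbalance shifts the estimate by 2 × 0.0635 × 2 = 0.25 points. That is about 0.3 of the standard error (0.25/0.888). It is a tail case built on assumptions, and the confidence interval and type I error rate already allow for chance imbalance.

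One gap on the plan's side remains. Protocol 1.14.3 leaves the details of missing-data handling to the SAP, but SAP 2.6.3 does not list the variables in the imputation model. The documents therefore neither include nor exclude these two.

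**Conclusion.** The point holds as an efficiency improvement. Baseline GDS is the only patient-level prognostic covariate in the primary model. QIDS-C and antidepressant use are available before allocation and could be added at almost no cost. The existing model is valid and the sample size is correct on its stated inputs.

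The likely size is small. With an assumed 0 to 5% of residual variance explained beyond baseline GDS, power rises from 80.0% by 0 to about 2 points and the standard error falls by at most 0.022 points (0.888 to 0.866). An assumed 10% would give about 84%. These figures depend on the plan's implied SD of 6.25, 99 evaluable patients per arm and an R² that the documents do not supply. The benefit for missing data is possible but not demonstrated.

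**What to change.** Before unblinding, amend the synopsis, protocol 1.14.3 and SAP 2.6.3 as follows.

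1. Add baseline QIDS-C (continuous) and baseline antidepressant use (yes/no) as fixed covariates in the primary model. For QIDS-C, specify the last value before randomisation, because Table 2 calls for a repeat at T0 when more than seven days have passed since screening.
2. State how antidepressant use is derived from the medication record. It cannot be read from the eligibility item, because no treatment and stable treatment both satisfy it. Protocol 1.13.3.1 specifies coding only for medical history and adverse events.
3. Name both variables in the multiple-imputation model.
4. Keep the present model, with baseline GDS as the only patient-level prognostic covariate, as a sensitivity analysis.

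The cost is two degrees of freedom, which is trivial with about 198 evaluable patients, plus a short coding rule and a slightly longer model statement. No new data are needed. If the sponsor prefers to leave the primary model unchanged, step 3 with the coding rule is the minimum worth doing, since the imputation variables have to be listed in any case.
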